**Methods/Design:**

A pilot weaning randomized controlled trial (RCT) is underway in the ICUs of 8 Canadian hospitals. We will randomize 90 critically ill adults requiring invasive ventilation for at least 24 hours and identified at an early stage of the weaning process to either Automated Weaning (SmartCare™) or Protocolized Weaning. The results of a National Weaning Survey informed the design of the Protocolized Weaning arm. Both weaning protocols are operationalized in Pressure Support mode, include opportunities for Spontaneous Breathing Trials, and share a common sedation protocol, oxygen titration parameters, and extubation and reintubation criteria. The primary outcome of the WEAN study is to evaluate compliance with the proposed weaning and sedation protocols. A key secondary outcome of the pilot RCT is to evaluate clinician acceptance of the weaning and sedation protocols. Prior to initiating the WEAN Study, we conducted a run-in phase, involving two patients per centre (randomizing the first participant to either weaning strategy and assigning the second patient to the alternate strategy) to ensure that participating centres could implement the weaning and sedation protocols and complete the detailed case report forms.

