### Objectives

The primary objective of the multicentre pilot study comparing SmartCare™ [hereafter referred to as "Automated Weaning"] and "Protocolized Weaning" is to evaluate compliance with the weaning and sedation protocols among intubated patients requiring > 24 hrs of invasive ventilation.

The secondary objectives of the multicentre pilot RCT are to evaluate clinician acceptance of the alternative weaning and sedation protocols using a Visual Analogue Scale daily, and to demonstrate the ability to recruit the desired patient population. In this manner, we will assess the feasibility of conducting a future, definitive weaning RCT in Canada.

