#### Study Outcomes

The primary outcome of the WEAN pilot study is compliance with the weaning and sedation protocols. Secondary outcomes include (i) daytime clinician (nurse; RRT and physician) acceptance of the sedation and weaning protocols, respectively, (ii) time to successful extubation defined as the time from randomization to unsupported (no requirement for NIV or invasive ventilation), spontaneous breathing for ≥ 48 hours after extubation (or disconnection with a tracheostomy), (iii) time to completion of a successful SBT, (iv) total duration of mechanical ventilation (time from intubation to termination of ventilation), (vi) ICU and hospital length of stay, (vii) ICU and hospital mortality, and the proportion of patients (viii) developing nosocomial pneumonia [39], (ix) with weaning (self-extubation, tracheostomy, reintubation and prolonged mechanical ventilation >21 days) or ICU (myocardial infarction and pneumothoraces) complications, and (x) requiring NIV. Any NIV use is considered clinically relevant.

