#### Data Collection

We collect data at ICU admission, study inclusion and daily thereafter. Whereas protocol violations (non compliance) in the Automated Weaning arm include return to/remain on an alternate mode of mechanical ventilation in the absence of meeting criteria and any unauthorized interruptions (cessations, manual increases/decreases) in the automated protocol, violations in the Protocolized Weaning group include unauthorized use of modes other than pressure support (i.e., assist control) without criteria to return to or remain on an alternate mode of mechanical ventilation. We tabulate a daily score reflecting the number of SBTs conducted divided by the number of required SBT assessments in which all criteria were met in the Protocolized Weaning group. Sedation protocol compliance is assessed by the percentage of daily SAS scores < 2 or > 5 (or alternatively, RASS scores < - 4 or > +1) in both arms. We also evaluate compliance with the PEEP/FiO_2 _chart in both groups. RRT and physician acceptance of the weaning protocols and critical care nurse acceptance of the sedation protocol is assessed daily using Likert [40] scales [ranging from 0 highly unacceptable (extremely difficult to use) to 10 highly acceptable (extremely easy to use)].

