#### Statistical Analyses

Descriptive statistics including means, standard deviations, medians, interquartile ranges and frequency distributions will be used to summarize the data. For univariate analyses, we will use the Chi-square test (alternatively, Fisher's exact test when the expected value is ≤ 5) and Student's t-test (alternatively, the Mann-Whitney U-test, if normality assumptions are not satisfied) for binary and continuous outcomes, respectively. We will evaluate the percentage of (i) hours off-protocol and (ii) daily SAS scores < 2 or > 5 (or RASS equivalent) by treatment group. Compliance will be considered acceptable if ≥ 75% [that is; protocol violations (off protocol hours without meeting criteria to return to/remain on an alternate mode of mechanical ventilation) or SAS scores < 2 or > 5 (equivalent RASS -4 < or > +1) occur < 25% of the time]. SBT compliance will be considered acceptable if ≥ 75% of SBT opportunities are realized. We will compare average Likert scale scores based on clinician group and the weaning strategy utilized using Analysis of Variance (ANOVA). We will compare time to successful extubation and death between groups using time-to-event analysis with censoring of deaths and application of the log-rank test. We will consider p-values ≤ 0.05 to be statistically significant.

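### The ANOVA of clinician acceptance confounds nurse contrasts with the protocol rated and ignores that scores on the same patient are correlated

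*Protocol article*

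**What the plan says.** The abstract of the protocol article gives the outcome its rank: "A key secondary outcome of the pilot RCT is to evaluate clinician acceptance of the weaning and sedation protocols". Study Outcomes assigns raters to protocols: "daytime clinician (nurse; RRT and physician) acceptance of the sedation and weaning protocols, respectively". Data Collection repeats the split and adds the frequency and the instrument: "RRT and physician acceptance of the weaning protocols and critical care nurse acceptance of the sedation protocol is assessed daily using Likert [40] scales", scored from 0 to 10. The abstract also says that the two weaning protocols "share a common sedation protocol, oxygen titration parameters, and extubation and reintubation criteria", and the Conclusion confirms that the sedation protocol is common to both arms.

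Statistical Analyses then fixes the method: "We will compare average Likert scale scores based on clinician group and the weaning strategy utilized using Analysis of Variance (ANOVA". The same section adds: "We will consider p-values ≤ 0.05 to be statistically significant". It does not define the unit over which scores are averaged. It names no patient, rater or centre term and no separate analysis by protocol rated.

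The Objectives section names a different instrument for the same outcome: "using a Visual Analogue Scale daily".

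**The concern.** The method has two factors, clinician group and weaning strategy, and neither fits the data as collected.

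- **Clinician group.** Its three levels do not rate the same thing. A lower nurse score could mean that nurses are harder to please, or that the sedation protocol is harder to use than the weaning protocols. The design cannot tell these apart.
- **Weaning strategy.** Nurse ratings concern a protocol that is the same in both arms. If they enter the arm contrast, the result is neither acceptance of the weaning strategy nor acceptance of the sedation protocol, but a blend of the two.

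Ordinary ANOVA also assumes independent observations. Here a patient contributes up to three scores, one per clinician group, each built from daily ratings. Scores that share a patient are likely to move together.

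The pilot is meant to inform a definitive trial, and acceptance is one of its stated feasibility questions. A spurious preference for one strategy, or a difference between professions that really compares two protocols, could mislead that planning.

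**Working it through.** **Step 1. Who rates what** (Study Outcomes and Data Collection).

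| Rater | Weaning protocol (differs by arm) | Sedation protocol (same in both arms) |
|---|---|---|
| Nurse | not rated | rated |
| RRT | rated | not rated |
| Physician | rated | not rated |

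Nurse versus either other group coincides exactly with sedation versus weaning protocol, so it is fully confounded. RRT versus physician is not, because both rate the weaning protocols. This step needs no assumption.

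**Step 2. What pooling nurses does to the arm contrast.** Suppose the true arm difference is d in RRT and physician scores and zero in nurse scores, with equal numbers of scores per group. The pooled arm difference is (d + d + 0)/3 = 2d/3. If nurse scores do differ by arm, the pooled figure is an average of two different quantities.

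**Step 3. Inputs for the error rates.** The article gives no power, effect size or standard deviation for acceptance, so there is no stated figure to reproduce. Alpha is 0.05, from Statistical Analyses, taken as two-sided. The number of ratings per patient (m) and the correlation (ρ) are not stated and are assumed. The formulas are:

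- Design effect for the arm contrast: DE = 1 + (m − 1)ρ.
- Actual type I error = 2 × [1 − Φ(1.96/√DE)].

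**Step 4. One average per patient and group, RRT and physician only (m = 2).**

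- ρ = 0.3: DE = 1.3; 1.96/√1.3 = 1.719; type I error 0.086.
- ρ = 0.5: DE = 1.5; 1.96/√1.5 = 1.600; type I error 0.110.

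The arm p-value is too small. The RRT versus physician contrast goes the other way. The variance of a paired difference is 1 − ρ times what the ANOVA assumes, so its error is 2 × [1 − Φ(1.96/√(1 − ρ))].

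- ρ = 0.3: 1.96/√0.7 = 2.343; type I error 0.019.
- ρ = 0.5: 1.96/√0.5 = 2.772; type I error 0.006.

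That p-value is too large.

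**Step 5. All three groups pooled, averaged first.** A simulation used 2000 runs per setting, 45 patients per arm (90 in total, 1:1 assumed), 1 + Poisson(3) daily ratings per patient and several splits of the patient variance. The pooled two-way ANOVA gave an arm type I error of 0.047 to 0.196 and a clinician-group error of 0.000 to 0.051. The arm error stays near 0.05 only where the groups share no patient effect.

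**Step 6. Raw daily ratings entered, one clinician group, m = 5.**

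- ρ = 0.2: DE = 1.8; type I error 0.144.
- ρ = 0.4: DE = 2.6; type I error 0.224.
- ρ = 0.6: DE = 3.4; type I error 0.288.

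With other assumptions the size changes: at ρ = 0.3, m = 2, 4 and 6 give 0.086, 0.155 and 0.215.

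**Step 7. After the fix.** In the same simulation, one average per patient with one clinician group at a time gave an arm error of 0.046 to 0.053. RRT versus physician as a paired comparison gave 0.046 to 0.054. Both are close to nominal.

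**The case against.** The strongest defence is the word average in the planned comparison. If scores are first averaged per patient within each clinician group, the daily repetition is gone, and one group at a time the arm test is valid. The article is condensed, and the averaging unit may be set in a document not shown. This stands against one tempting inference: a reader might conclude that raw daily ratings are treated as independent and that the error is 14% to 29%. The text does not say so, and that range is conditional. The defence does not rescue the stated method, however. With clinician group as a factor, each patient still gives two or three correlated scores after averaging (Steps 4 and 5).

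Three other stronger readings are not supported.

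- *The clinician-group comparison is meaningless, or all its p-values are too small.* RRT versus physician can be interpreted, and its p-value tends to be too large.
- *Grouping by the strategy utilized means as-treated analysis.* The sections on suspending weaning and on reintubation keep patients on the assigned strategy or return them to it. No crossover is described, so the word is probably loose.
- *The same clinicians rate many patients.* This is plausible but not stated, and its effect on the arm contrast cannot be determined from the text.

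It is also fair to say that acceptance is secondary, that it has no acceptability threshold such as the 75% set for compliance, and that no decision is tied to its p-value. That limits the severity.

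**Conclusion.** The point holds in a limited form. That nurse contrasts are confounded with the protocol rated follows from the article's own text without any assumption. So does the mixing of a shared protocol into the arm contrast if nurses are pooled with the others.

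The size of the dependence problem rests on assumed correlations. With one average per patient and group, the nominal 5% arm test on RRT and physician scores runs at about 8.6% to 11.0%, and the RRT versus physician test is conservative. The larger range of 14% to 29% applies only if raw daily ratings enter the model. Clustering by rater and centre was not quantified.

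Severity is low to moderate: the stated method does not fit the data, but it concerns a secondary outcome of a pilot. The two names for the instrument are a minor inconsistency that does not bear on the ANOVA.

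**What to change.** Replace the ANOVA sentence in Statistical Analyses with the following elements:

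1. Analyse RRT and physician ratings of the weaning protocols in one model and nurse ratings of the sedation protocol in another, each by randomized arm.
2. In each model, use either one mean per patient per clinician group or a mixed model on the daily ratings with a random effect for patient, and account for centre. If means are used, the weaning model must still link the RRT and physician means of the same patient.
3. Treat RRT versus physician as a within-patient contrast.
4. Drop formal comparisons of nurses with RRTs or physicians, and report nurse scores descriptively beside the others.
5. Use one name for the acceptance scale in Objectives, Data Collection and Statistical Analyses.

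The cost is a change of wording. The data collected, the sample size and the case report forms stay the same, apart from confirming which scale the forms actually use.

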#### Spontaneous Breathing Trials

Since patients who successfully complete a PST include those who *do *and *do not *require further weaning, we conduct an SBT with the goal of identifying patients who can tolerate pressure support but *fail *an SBT. These individuals are regarded as requiring further weaning. We consider patients with (i) partial or complete reversal of the cause of respiratory failure with SpO_2 _≥ 90% on an FiO_2 _≤ 0.4 (or at baseline level in chronically hypoxemic patients) and PEEP ≤ 5 cm H_2_O, (ii) hemodynamic stability [off vasopressors or on low levels of vasopressors (i.e., levophed ≤ 7 µg/min or ≤ 0.1 µg/kg/min) or equivalent], (iii) absence of uncontrolled sepsis, and (iv) stable haemoglobin > 70 g/L to undergo a SBT. We conduct SBTs of 30 to 120 minutes duration using either a T-piece with oxygen or continuous positive airway pressure (CPAP) ≤ 5 cm H_2_O or PSV of 5 - 7 cm H_2_O (using a heated humidifier or alternatively, 10-12 cm H_2_O with a heat and moisture exchanger) [27,30] with or without 5 cm H_2_O PEEP. Patients who successfully complete a SBT are considered for extubation (i.e., do not require further weaning). Conversely, patients who fail a SBT are randomized. We consider the presence of any one of the following: (i) RR > 35 breaths/min, (ii) clinical signs of respiratory distress (i.e., abdominal paradox), (iii) SpO_2 _< 90% (or below baseline in chronically hypoxemic patients) with FiO_2 _> 50%, (iv) systolic blood pressure ≤ 80 mmHg or ≥ 180 mmHg, (v) heart rate ≤ 50 or ≥ 140 beats/min or new significant dysrhythmias, (vi) severe agitation or diaphoresis, or (vii) Increased somnolence with elevated arterial pressure of carbon dioxide (PaCO_2_) and pH < 7.30 to signify SBT failure. In summary, we randomize consented patients requiring pressure support of at least 10 cm H_2_O who (i) successfully complete a PST, but DO NOT meet criteria to undergo a SBT (i.e., are too early to undergo a SBT) or (ii) who successfully complete a PST and fail a SBT.

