#### Weaning Procedures

Randomized patients are initiated on either the Automated Weaning or Protocolized Weaning algorithms until extubation criteria are achieved. All patients will be followed until successful extubation, ICU death, ICU discharge or until 90 days after randomization (deemed ventilator dependent).

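### The only stated analysis that reaches time to a successful SBT is the t-test or Mann-Whitney test, which has no value to use for patients who never pass one

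*Protocol article*

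**What the plan says.** All references are to the protocol article.

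- **Study Outcomes** lists the outcome among the secondary outcomes, directly after time to successful extubation: "iii) time to completion of a successful SBT".
- **Statistical Analyses** names the outcomes that get survival methods: "We will compare time to successful extubation and death between groups using time-to-event analysis". Deaths are to be censored and the log-rank test used. Time to a successful SBT is not named.
- The same section gives a general rule that pairs binary outcomes with the Chi-square or Fisher test and continuous outcomes with "Student's t-test (alternatively, the Mann-Whitney U-test, if normality assumptions are not satisfied) for binary and continuous outcomes, respectively". No other sentence could apply to a time to SBT. No value, rank or censoring rule is given for a patient who never passes.
- **Weaning Procedures** sets the end of follow-up: "All patients will be followed until successful extubation, ICU death, ICU discharge or until 90 days after randomization (deemed ventilator dependent".
- **Study Outcomes** expects some unplanned ends to ventilation, since one outcome is the proportion of patients "with weaning (self-extubation, tracheostomy, reintubation and prolonged mechanical ventilation >21 days".
- **Spontaneous Breathing Trials** describes the two routes into randomization. Patients are either too early for an SBT or are those "who successfully complete a PST and fail a SBT".

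**The concern.** Time to a successful SBT is the same kind of variable as time to successful extubation: it starts at randomization and some patients never reach it. The protocol treats the two differently and gives no reason.

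A t-test or Mann-Whitney test compares observed numbers. With no rule for patients who have none, the analyst is left with those who passed. Passing happens after randomization and may be affected by the assigned strategy, so the two groups of passers are no longer the randomized groups. If one strategy gets additional difficult patients through an SBT, and they pass late, it adds long times to its own arm. The other arm's equivalent patients contribute nothing.

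The outcome matters because completing an SBT is a milestone the automated system is built to reach, and the pilot is meant to inform a definitive trial.

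**Working it through.** **1. Which rule applies.** Outcome (iii) is not in the time-to-event sentence, is not binary and is not an acceptance score (those go to ANOVA). That leaves the rule for continuous outcomes.

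**2. Whether patients without a value can occur.** Entry requires having failed an SBT or being too early for one, so nobody has passed at randomization. Follow-up can end by ICU death, ICU discharge or day 90, and self-extubation is a listed complication. Each can happen before any SBT is passed.

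**3. Mechanism, by arithmetic.** The protocol gives no pass rates, so every input here is an assumption:
- In both arms 70% pass at exponential times with median 2 days.
- In arm A a further share x pass at times uniform on days 8 to 20. Their counterparts in arm B never pass, so arm A is better.

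The chance that an ordinary time exceeds a late time is the average of 2^(−t/2) over days 8 to 20: (2/ln 2) × (2^−4 − 2^−10) / 12 = 2.885 × 0.0615 / 12 = 0.015.

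Chance that a random arm A patient passes earlier than a random arm B patient (0.5 means no difference):
- Passers only: [0.70 × 0.5 + x × 0.015] / (0.70 + x)
- All randomized, never passing ranked last: 0.70² × 0.5 + 0.70 × 0.30 + 0.70 × 0.015x + 0.30x + 0.5 × 0.30 × (0.30 − x)

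| Extra passers x | Passers only | All randomized |
|---|---|---|
| 0 | 0.500 | 0.500 |
| 5% | 0.468 | 0.508 |
| 10% | 0.439 | 0.516 |
| 20% | 0.392 | 0.532 |

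For x = 20%: passers only (0.350 + 0.003) / 0.90 = 0.392; all randomized 0.245 + 0.210 + 0.002 + 0.060 + 0.015 = 0.532. The passers-only figure falls below 0.5 although arm A is better.

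**4. Size in a trial of 90.** The same assumptions were simulated with 45 per arm (the allocation ratio is not stated) and the protocol's threshold, "We will consider p-values ≤ 0.05 to be statistically significant", taken as two-sided. The test is Mann-Whitney on passers only.

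| Extra passers in A | A's median longer by | Significant, A slower |
|---|---|---|
| 0 | about 0 days | about 2.5% (chance level) |
| 5% | about 0.2 days | about 6% |
| 10% | about 0.5 days | about 13% |
| 20% | about 1.1 days | about 35% |

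A log-rank test on all randomized patients, with non-passers kept at risk to day 90, favoured A on average: mean Z of 0.32, 0.66 and 1.31 for 5%, 10% and 20%. It was significantly wrong in 1.3%, 0.7% and 0% of trials.

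**5. Sensitivity to the assumptions.**
- If arm A also halves the ordinary passers' median from 2 days to 1, the wrong-direction rate with 20% extra passers falls to about 1%, and the right-direction rate is only about 4% to 5%.
- With 80% against 90% passing and the same speed-up, the wrong-direction rate is 0% and the right-direction rate about 29% to 30%.
- A different set-up assumed 20% to 40% hard-to-wean patients per arm, passing at 8 days plus an exponential time with mean 7 days, and ordinary passers with mean 3 days. The better arm had the longer mean among passers in 72% to 95% of trials. With equal passing there was no bias.
- In that set-up, with 30% hard-to-wean patients of whom 90% against 30% pass, the log-rank mean Z was +0.99 with non-passers censored at exit and +1.42 with them kept to day 90. Simple censoring therefore discards part of the real difference.

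**The case against.** **The article does not state the exclusion.** A reader might infer that the plan explicitly sends this outcome to a t-test and drops non-passers. It says neither. Both follow from a general rule plus the absence of any other, and a Mann-Whitney test with non-passers ranked worst would avoid the problem, though none is described. A condensed article may also leave such detail to a fuller document. This limits how firmly the point can be put. It does not remove the point, because the section does allocate methods: it names the outcomes for survival analysis, leaves this one out and supplies a default that does not fit it.

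**Death or day 90 does not imply a missing value.** A reader might assume that every patient who dies ventilated or is still ventilated at day 90 lacks an SBT time. The protocol does not support that. Passing an SBT leads only to consideration for extubation, and reintubation is provided for, so some of these patients will have passed earlier. Only those who never passed are affected, and their number is unknown.

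**The direction is not fixed.** A reader might conclude that the arm that gets more patients through an SBT will look slower. That needs unequal passing, with the extra passers late. The Background cites earlier recognition of SBT readiness as a property of the automated system, and a speed-up of that kind can cancel or outweigh the bias. This stands, and the 35% figure should not be quoted alone.

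**The stakes are limited.** This is one secondary outcome of a feasibility pilot. Time to successful extubation already has a log-rank test, and no compliance threshold depends on the SBT time. This also stands.

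**Conclusion.** The point holds in limited form. As written, outcome (iii) is reached only by a method that cannot use patients who never pass an SBT, and the design allows such patients in several ways. Followed literally, the comparison is conditional on a success after randomization and can mislead when pass rates differ by arm.

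The protocol does not allow the size to be fixed. The illustrative range runs from no bias with equal passing, through about 6%, 13% and 35% wrong-direction significance with 5%, 10% and 20% late extra passers, to about 1% at 20% extra passers when ordinary passers are also speeded up. These figures rest on assumed pass rates, assumed time distributions and 45 patients per arm. The primary conclusion on compliance does not change.

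**What to change.** Add time to a successful SBT to the outcomes given a time-to-event analysis, in its own clause so that it does not inherit the censoring of deaths:

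- Analyse all randomized patients from randomization to the first successful SBT.
- Treat death without a successful SBT as a competing event, so that the patient is kept as never having the event. Censor at day 90.
- State in advance how ICU discharge without a successful SBT is handled.
- State in advance how extubation without a successful SBT, including self-extubation, is handled. One option is a competing event in the main analysis, with a sensitivity analysis that counts it as a success. Counting it as a success in the main analysis would change the endpoint and move it towards time to successful extubation.
- Say that the t-test and Mann-Whitney rule does not apply to this outcome.

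The cost is a few sentences and a different analysis routine. Extubation, death and ICU stay are already needed for other outcomes. The Data Collection section does not mention SBT completion times, and its daily SBT score covers only the Protocolized arm, so the sponsor should confirm that the time of the first successful SBT is recorded in both arms. The listed outcome requires that in any case.

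### The sentence that censors deaths should be split: it does not fit the death comparison, and for time to extubation it leaves death as an unhandled competing event

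*Protocol article*

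**What the plan says.** The Statistical Analyses section of the protocol article will compare "time to successful extubation and death between groups using time-to-event analysis with censoring of deaths", and applies the log-rank test. It gives no other censoring rule for death and names no competing-risk method.

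Study Outcomes lists as secondary outcomes "time to successful extubation defined as the time from randomization to unsupported" breathing sustained for at least 48 hours, and separately "ICU and hospital mortality". Time to death is not in that list; it appears only in the analysis sentence.

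Weaning Procedures sets the end of follow-up: "All patients will be followed until successful extubation, ICU death, ICU discharge or until 90 days after randomization (deemed ventilator dependent". ICU death therefore closes a patient's record before extubation can occur.

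**The concern.** The sentence names two endpoints and attaches one rule to both. In the death analysis, the event of interest would be the thing that is censored. In the extubation analysis, a patient who dies before success leaves the risk set as if still able to be extubated later. Reading the result as the chance or timing of extubation assumes that those who died would have had the same later prospects as those still ventilated.

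At stake is how the between-arm comparison of extubation is interpreted. If deaths before extubation differ between arms, the proportion who are successfully extubated differs too, and the planned test is not built to show it.

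**Working it through.** **Inputs.** From the article: log-rank test with deaths censored; a day-90 horizon; 90 patients; "We will consider p-values ≤ 0.05 to be statistically significant". Assumed: 45 per arm (allocation ratio not given), a two-sided test (sidedness not given), constant hazards, and 10% to 40% of patients dying before extubation. The time scale is also assumed: an extubation hazard with a 4-day median, borrowed from the usual-care duration that the Background reports for the European trial.

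**1. The plan's own figure.** There is none to reproduce. The Sample Size section gives no event count or power for these endpoints.

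**2. Death, read literally.** With every death censored, the number of events is d = 0 at all times. The log-rank numerator Σ(d₁ − d·n₁/n) is 0 and its variance is 0, so the statistic is undefined.

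**3. Proportion extubated.** Let a be the extubation hazard, b the hazard of death before extubation, and m the share dying first.

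- a = ln 2 / 4 = 0.173 per day; b = a·m/(1 − m)
- Deaths censored: 1 − KM(t) = 1 − exp(−a·t)
- Death as competing event: CIF(t) = a/(a + b) × [1 − exp(−(a + b)·t)]

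Example for m = 20%, day 21: b = 0.173 × 0.2/0.8 = 0.043. Then 1 − KM = 1 − exp(−3.64) = 97.4%, and CIF = 0.8 × [1 − exp(−4.55)] = 79.2%. The gap is 18 points.

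| Dying first | Day 21: 1 − KM | Day 21: CIF | Gap (points) | Day 90: 1 − KM | Day 90: CIF | Gap (points) |
|---|---|---|---|---|---|---|
| 10% | 97.4% | 88.4% | 9 | about 100% | 90% | 10 |
| 20% | 97.4% | 79.2% | 18 | about 100% | 80% | 20 |
| 30% | 97.4% | 69.6% | 28 | about 100% | 70% | 30 |

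By day 90 almost every record has ended, so the gap is simply the share dying first.

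**4. What the test responds to.** Simulation of 45 per arm, 1,500 runs per scenario. The planned test is compared with a log-rank test that keeps patients who die in the risk set to day 90 as not extubated.

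| Extubation hazard ratio | Dying first, by arm | Rejects, deaths censored | Rejects, deaths kept as not extubated |
|---|---|---|---|
| 1.0 | 20% vs 20% | 6.1% | 5.3% |
| 1.0 | 10% vs 20% | 4.7% | 14.5% |
| 1.0 | 10% vs 30% | 4.8% | 42.3% |
| 1.0 | 20% vs 40% | 5.5% | 34.3% |
| 1.5 in the arm with more deaths | 10% vs 30% | 34.9% | 17.4% |

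Simulation error near 5% is √(0.05 × 0.95/1,500) = 0.6 points. With equal extubation hazards, the planned test therefore holds its level approximately and does not respond to the mortality difference. In the last row, extubation by day 90 is 90% vs 70%. The planned test favours the arm with more deaths in 34.8% of runs; the other version does so in 0.3%. The planned test is not wrong there, since that arm does have the higher extubation hazard. It answers a different question.

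**The case against.** **The death analysis is not really impossible.** Because the sentence names death as something to compare, a sensible analyst would censor deaths in the extubation analysis only. That is probably what was meant, and the death analysis can then be run. What stands is that the text does not say it and gives death no censoring rule of its own.

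**The log-rank test is valid.** With deaths censored it tests the cause-specific extubation hazard, and the simulation supports its level. The article promises no Kaplan-Meier curve and no probability of extubation, so the overstatement arises only if such a curve is drawn or the result is read that way. Preferring cumulative incidence is partly a choice of estimand. This stands in full, and it is why the existing test should be kept as a companion.

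**Mortality is not hidden.** A reader might infer that an arm with more deaths could pass unnoticed. The article does not support that: ICU and hospital mortality are separate outcomes, and death is also compared between groups.

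**The death rate is assumed.** The exclusions for anticipated withdrawal of life support and for poor neurological prognosis after cardiac arrest, together with the required pressure support trial, could make early death less common than assumed. At 5% dying first, the day-90 gap would be about 5 points.

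**Conclusion.** The point holds as a correction that should be made to the analysis of secondary outcomes. The sentence cannot be applied to both endpoints as worded. For extubation, it yields a comparison of hazards among patients still alive and ventilated, not of the chance of successful extubation. A Kaplan-Meier complement from it would be too high at day 90 by about the share dying first: 10 to 30 points under the assumed range and constant hazards. The simulated rejection rates rest on the same assumptions and on 45 per arm.

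Two wider readings are tempting but not supported. A reader might infer that the other durations (time to a successful breathing trial, total ventilation, length of stay) go to the t-test or "the Mann-Whitney U-test, if normality assumptions are not satisfied", so that early deaths count as short, good durations. That rule is generic for continuous outcomes; the article does not assign those durations to it. A reader might also infer that these outcomes will carry over into the definitive trial. The article says that the pilot informs feasibility through compliance, acceptance and recruitment, and does not name the later trial's endpoints.

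**What to change.** Replace the sentence with two analyses.

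1. **Time to successful extubation.** Treat death before success as a competing event. Show cumulative incidence by arm with Gray's test, or keep patients who die in the risk set to day 90 as not extubated. Report the deaths-censored log-rank test or the cause-specific hazard ratio beside it.
2. **Time to death.** Make death the event, do not censor at extubation, and state the end of follow-up. The general follow-up rule stops at successful extubation, whereas hospital mortality needs observation beyond it. If observation ends at hospital discharge, say how patients discharged alive are handled.

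The cost is rewording and a few lines of code. The dates of extubation, death and discharge are already needed for the listed outcomes; only a death horizon beyond hospital discharge would call for more data. The downside is a second estimate to interpret and lower apparent extubation proportions.
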